# Med. 1992;11(10):1305-19.

# WP 5: Associations between early language and motor skills

### Background

The development of early language skills and other cognitive and social skills are correlated in early childhood and have been linked to later academic achievement in numerous studies (for a review see, La Paro & Pianta, 2000). However, the association between motor and language development is not well understood.

In preschoolage and slightly older children, most studies have assessed the role of motor abilities in children with specific language impairment (SLI). Studies have demonstrated that in children with SLI, gross motor skills development is significantly correlated with auditory comprehension, impressive and expressive language skills, and articulation, which collectively indicate a complex relationship between motor and language skills in these children (3, 8, 10). Studies have also demonstrated strong associations between early motor and language development in children with dyslexia (6, 7)

The majority of studies in the general populations have been conducted with infants. A recent systematic review identified 17 studies which demonstrated in different ways significant relationships between the development of motor skills and language and social interactions in typically developing children aged between 1 and 3 years (2). For instance, two large populationbased cohort studies found that in particular fine motor skills and communications skills were significantly correlated and that early motor skills most strongly predicted later communication skills (9) and that infants with minor deviances from normal neuromotor development had a somewhat higher risk of being language delayed (5). There are relatively few studies in typically developing preschoolage children. A study by Cheng et al. (2009) indicated that in 5- 6 year old children motor skills accounted for a significant amount of variance in language measures.

Similarly, a study of 3-6 year old children found that fine motor skills appeared to be the most correlated with language skills, but at 3 and 4 years gross motor skills were also correlated with receptive and expressive language skills (4).

Current findings therefore suggest in particular an association between fine motor skills and language development in typically developing children and that poor or atypical motor development could be an important contributing factor to early language delay. The high correlation and the predictive value of early motor skills on later language development are often interpreted as evidence that motor and language difficulties are two manifestations of a common underlying neurodevelopmental weakness but the relationship between language and motor skills is probably complex and multifaceted (9, 3). However, the findings are based on relatively few studies, in particular in preschoolage children, and the association with long-term reading outcomes has mainly been studied in children with dyslexia. More longitudinal research based on a populationbased sample is therefore needed. Given the associations between language and motor development, a motor performance programme may have impact on language development.

However, existing intervention studies mix language and physical activities (e.g. 1) in a way that it is not possible to measure the specific impact of the motor performance activities on language development.

### Aim

To examine associations between early language and motor skills in typical and atypical children aged 3-5 years and to investigate whether a motor skill intervention can improve language and pre-literacy development in preschool children.

### Objectives to be explored in the RCT

1. To estimate the effect of a motor skills intervention on language and pre-literacy development in preschool children

### Objectives to be explored in the cohort study

1. To determine the cross-sectional association between language and pre-literacy development in preschool children and parent and child characteristics
2. To determine the cross-sectional association between language and pre-literacy development and motor performance in typical and atypical children from age three to six.
3. To establish potential patterns of development of language/pre-literacy development, and motor performance and later reading development from three to fifteen years of age.

### Variables

Outcome:

*Language and pre-literacy development.*

The language and pre-literacy skills of children will be assessed using *Language assessment 3-6* (LA; Bleses et al., 2015) which is administered by the preschool teachers. The assessment battery consists of measures within two domains of language, i.e. oral language (Vocabulary, Comprehension, Communication strategies) and pre-literacy measures (Rhyme detection, Print awareness, Deletion and Letter identification). With the exception of Communication, children will be directly assessed via picture identification or picture elicitation tasks. A validation study shows acceptable data characteristics according to the criteria for the Rasch model for the subscales. Internal consistency coefficients (Cronbach’s alpha) for subscales were between .75-.91; correlations between subscales were between .25-.70. The concurrent correlations of the language subscales with The Peabody Picture Vocabulary Test-4 (PPVT-4, Dunn and Dunn, 2012) were .55 for Vocabulary and .57 for Comprehension; correlations with the Expressive Vocabulary Test 2 (EVT-2, Williams, 2007) were .42 for Vocabulary and .39 for Comprehension. For the pre-literacy subscales, the correlations with PPVT-4 were .33 for Rhyme detection, .49 for Deletion, and .39 for Letter Identification; the correlations with EVT-2 were .18 for rhyme, .29 for Deletion, and .33 Letter Identification.

*Reading measures.* The Danish National Tests includes ten mandatory tests in six subjects, administered individually to children from Grade 2 to Grade 8, offering the opportunity to follow academic achievement of Danish children through the period of compulsory schooling. The reading measure from The Danish National Tests in Grades 2, 4, and 6 will be used. The Danish National Tests in reading evaluate students’ reading ability within three areas: Language comprehension (semantics of individual words, homonyms, language use, idioms), Decoding (word identification in concatenated words, word reading), and Reading comprehension (comprehension of written texts). The Danish National Tests provide a valid estimate of student abilities (Beuchert, & Nandrup 2014). For example, lower scores are associated with low birth

weight, special education needs and low socioeconomic status; all together student and parental background explained approximately 13-21% of the variance in performance. The grade 9 school examinations provided an external measure of validity; when they were regressed on the same-subject national test data, the earlier national test results explained 48-49% of the Danish and math examination marks (Beuchert & Nandrup, 2014).

### Covariates

The following covariates will be accounted for when analysing the results: Sex, age, socioeconomic status, motor development.

### Length of follow-up

The duration of the follow-up will be 12 years which cover three years in preschool and nine years in school.

### Analyses

Cross-sectional analyses will be conducted using multilevel linear regression to determine the association between language and literacy skills and motor development after adjusting for age, gender and SES level.

Multilevel linear regression analysis will be used to determine the prediction from the early language and literacy measures, together with age, gender, and SES, to the three educational outcomes of Language comprehension, Decoding, Reading comprehension, taken from the National Test. The regression analysis determined the effect of age, sex and SES on mean levels of performance, as well as evaluating the unique variance contributed by early language, literacy motor performance and SES.

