### Perspectives

The project will reveal new insights into the relationship between early language and pre-literacy development and motor development in both typical and atypical populations, and the development of language/pre-literacy development, and motor performance and later reading development from three to fifteen years of age. The findings may enable recognition of related risk patterns in both language and motor development and affect interpretations of screening test results of early language delay (e.g. in relation to the mandatory language screening of three-year old children in Denmark) and the planning of early (and possible more targeted) interventions for those at risk of motor and language difficulties. The RCT has the potential to show the effect of a motor performance programme on language development in particular in children at risk of language delay. Together, this opens ‘a window of opportunity’ for implementing more global early interventions in daycare centres.

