### Analyses

The analytic strategies described in the other WPs will be repeated on the subgroup of children who are identified as having early developmental difficulties.

For the cohort study, longitudinal latent class analysis and latent class growth analysis will be conducted to describe the patterns of developmental difficulties.

To describe barriers to, and facilitators of, implementation of the motor skills intervention for children at early developmental risk, observations and interviews are analyzed using a phenomenological analytic approach [14] to understand the participation of the child.

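### WP 5 states a randomised objective for language and pre-literacy, but its Analyses section specifies only association and prediction models without an intervention-group term

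*Protocol*

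**What the plan says.** WP 5 puts one item under its objectives for the RCT: "To estimate the effect of a motor skills intervention on language and pre-literacy development in preschool children". The Aim carries the same causal question: "to investigate whether a motor skill intervention can improve language and pre-literacy development in preschool children". The Perspectives section expects an answer: "The RCT has the potential to show the effect of a motor performance programme on language development". The outcome instrument is named under Variables: "The language and pre-literacy skills of children will be assessed using" the Language assessment 3-6, given by preschool teachers.

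The Analyses section then describes two models. The first: "Cross-sectional analyses will be conducted using multilevel linear regression to determine the association between language and literacy skills and motor development", adjusted for age, gender and SES. The second: "Multilevel linear regression analysis will be used to determine the prediction from the early language and literacy measures, together with age, gender, and SES", where the outcomes are three reading measures from the Danish National Tests. The same regression is also meant for "evaluating the unique variance contributed by early language, literacy motor performance and SES".

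The WP 5 Covariates section lists sex, age, socioeconomic status and motor development. It gives no time point for motor development and does not mention allocation.

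WP 8 includes language among the outcomes of its first RCT objective, for children at early developmental risk. Its Analyses section says: "The analytic strategies described in the other WPs will be repeated on the subgroup of children" identified as having early developmental difficulties.

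**The concern.** A randomised objective needs a contrast between the randomised groups. The WP 5 Analyses section does not merely leave such a model short of detail. It fixes two analyses, and both answer other questions. An analyst who follows it exactly will estimate how language varies with motor skill across all children, and how early language predicts later reading. Either could be estimated in a cohort with no intervention.

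At stake is whether WP 5's only RCT question has a prespecified answer. If no between-arm model is fixed before the data are seen, several choices stay open: which language score, which follow-up, and which covariates. The undated motor-development covariate adds a specific hazard. Someone assembling the missing model from WP 5's own text could adjust for motor skill measured after the intervention began, which is what the intervention is meant to change.

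**Working it through.** The plan gives no sample size, power or effect size for WP 5, and the point rests on none. The check sets objectives against models.

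**Terms in the WP 5 models, as written**

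- Model 1: language or literacy score = b0 + b1 × motor development + b2 × age + b3 × gender + b4 × SES, multilevel. The coefficient of interest is b1, the difference in language per unit of motor skill between children. There is no arm term.
- Model 2: reading score (language comprehension, decoding or reading comprehension) = c0 + c1 × early language + c2 × early literacy + c3 × age + c4 × gender + c5 × SES, with motor performance also considered for its unique variance. Language is a predictor here, not the outcome. There is no arm term.

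**Match to the WP 5 objectives**

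- RCT objective (effect on language and pre-literacy): no model.
- Cohort objective 2 (cross-sectional language–motor association): Model 1.
- Cohort objective 3 (developmental patterns and later reading): Model 2, in part.

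Tally: 1 RCT objective, 2 models, 0 with intervention group. Neither model includes a baseline language score or time since baseline, so neither becomes an effect model on a generous reading.

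**Is the comparison supplied elsewhere in the file?**

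| Work package | Outcomes with a between-arm model | Language or pre-literacy? |
| --- | --- | --- |
| WP 1 | Motor skills; parents' perception of motor competence | No |
| WP 3 | Aberrant movement; number of MSK diagnoses | No |
| WP 4 | Physical activity; adiposity | No |
| WP 6 | Psychological, physical and emotional wellbeing; self-esteem | No |
| WP 7 | Executive functioning; academic performance by Grade 9 grades | No |
| WP 8 | Repeats the strategies of the others | Nothing to repeat for language |

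The WP 7 academic model comes nearest, but its outcome is a school-leaving grade, not preschool language. The WP 1 model is written for motor outcomes by name, and WP 6 and WP 7 each write out their own model in full instead of relying on it. Nothing in WP 5 points to WP 1.

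**The covariate list**

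If a between-arm model were built with WP 5's listed covariates, motor development would enter it. Entered at baseline, it is an ordinary prognostic covariate. Entered at follow-up, it lies on the route by which motor training is supposed to influence language. The group coefficient would then exclude whatever part of the effect passes through motor skill. The section does not say which value is meant.

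**The case against.** The strongest objection concerns reach. This file is an additional file to a main protocol that is not shown, and it defers to that protocol for the intervention, the motor test and the follow-up figure. A SAP may also exist. Either could hold a general between-arm model that covers language. A reader might infer from this file that the arms will never be compared on language, or that any such comparison will be post hoc. The document does not support that. It shows only that no such comparison is specified here.

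Second, the other work packages are not complete either. WP 1 names no model for the child's own perceived competence, WP 3 none for parent-reported pain by arm, and WP 4 none for sports participation by arm. The Analyses sections are evidently summaries, so silence on one outcome is weak evidence that nothing is planned. This stands as a caution. WP 5 still differs in kind: of the work packages that state an RCT effect objective and write out their own models, it is the only one with no between-arm model at all.

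Third, analysis detail is commonly left to a SAP. That would excuse an unspecified model. It does not excuse an Analyses section that is specified and answers a different question from the RCT objective a few paragraphs above it.

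Fourth, nothing here touches the primary outcome. That is correct and limits the severity.

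**Conclusion.** The point holds for this file. WP 5's sole RCT objective has no matching analysis: neither of the two stated models contains intervention group, and no between-arm model for language appears in any other work package. The gap carries over to the language part of WP 8's first RCT objective. Followed as written, WP 5 would yield an observational association and not its randomised effect.

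This should be fixed, but it does not threaten the trial's main conclusion. The primary outcome, MovementABC-2 at 18 months, has its own between-arm model in WP 1. A reader might go further and expect the motor–language association to be reported as proof that training improves language. Nothing in the document says that it will be.

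No numerical size is attached. WP 5 gives no sample size, cluster count or intracluster correlation, and a power figure would not bear on whether the model is there. The conclusion assumes only that the text shown is WP 5's full analysis section in this file.

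**What to change.** 1. In WP 5, Analyses, put a between-arm model ahead of the existing two, in the form used in WP 1 and WP 6: multilevel linear regression of the preschool follow-up Language assessment 3-6 score on intervention group, baseline score of the same scale, time since baseline, age, sex and SES, with preschool as a random effect.
2. Name the follow-up at which this is assessed, and name the primary language score. The instrument has 3 oral-language and 4 pre-literacy measures, 7 in all, and the section does not say which one, or what combination, carries the objective.
3. In WP 5, Covariates, state that only baseline motor development may enter the between-arm model, and that motor skill at follow-up may not.
4. Label the two existing models as cohort analyses. WP 8 then has a usable language model to repeat.
5. If the main protocol or a SAP already holds a between-arm model that covers language, a cross-reference to it can replace item 1; items 2 to 4 still apply unless they are settled there.

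The cost is a paragraph of text and one extra model per language score. No new data are needed provided the language assessment is repeated at follow-up. The RCT objective implies this, but WP 5 gives no assessment schedule, so it should be confirmed.

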### Perspectives

The project will reveal new insights into the relationship between early language and pre-literacy development and motor development in both typical and atypical populations, and the development of language/pre-literacy development, and motor performance and later reading development from three to fifteen years of age. The findings may enable recognition of related risk patterns in both language and motor development and affect interpretations of screening test results of early language delay (e.g. in relation to the mandatory language screening of three-year old children in Denmark) and the planning of early (and possible more targeted) interventions for those at risk of motor and language difficulties. The RCT has the potential to show the effect of a motor performance programme on language development in particular in children at risk of language delay. Together, this opens ‘a window of opportunity’ for implementing more global early interventions in daycare centres.

# WP 6: Association between motor skills and wellbeing

**Background**

Motor skills contribute to children’s physical, cognitive and social development [1]. However, the relationship between motor skills and wellbeing has been less investigated, with most studies focusing on the relationship between poor motor skills and wellbeing [2]. Poor motor skills have been associated with fewer playmates, fewer spare-time activities, less time spent engaged in social activities and symptoms of anxiety and depression [2]. Motor skills are further seen as an important foundation for participation in physical activities [3] and level of physical activity [1], which has been linked to mental health, wellbeing and fewer emotional and social problems [2-5]. Studies of physical activity or exercise programs indicate improvements in mood, prevention of depression and reduction in depression and anxiety symptoms [4]. The importance of regular motor skills training in preschool children in terms of wellbeing has, to our knowledge, not been investigated previously. In general, there is a need for studies with large sample sizes that follow development for a longer period of time in order to investigate both the short-term and the potential long-term effects of a motor skills intervention on child wellbeing from a developmental perspective [2,4].

Wellbeing is a multi-faceted concept involving physical, psychological, cognitive, social and economic domains. Wellbeing is influenced not just by contextual and individual factors in these domains but also the child’s perception of these factors [5,6]. The motor skills intervention as described in the main body of the application is directed towards improvement in motor skills, but as the intervention is integrated with the preschool curriculum, the intervention may also influence peer interactions and staff-child interactions, both in the introduced motor skills activities and in other more familiar activities. Similarly, the children may experience new opportunities for participation in activities in preschool with the possibility of changes in self-perception.

A prophylactic strategy focusing on improving motor skills activities in preschool children may therefore have the potential to improve the current and future physical, psychological and social wellbeing and their associated health benefits. Based on previous research on poor motor skills and wellbeing, the effect of motor skills training may be stronger for children who are initially characterized by poor motor skills.

### Objectives to be explored in the RCT

The objective is to estimate the effect of a motor skills intervention on wellbeing.

### Objectives to be explored in the cohort study*

- 1. To establish potential patterns of development of psychological wellbeing from three to fifteen years of age.
  2. To determine the influence of motor skills and physical activity in preschool on psychological well-being in adolescence.

** long-term follow-up (12 years)*

### Variables

*Predictors:*

- Motor skills as described in the main application
- Physical activity as described in WP 4

*Outcomes:*

Psychological wellbeing will be measured using the Strengths and Difficulties Questionnaire (SDQ) [7- 9]. The SDQ is a brief questionnaire measuring child and adolescent psychological wellbeing. The SDQ includes 25 items, divided into 5 scales (5 items each): 1) emotional symptoms, 2) conduct problems,

3) hyperactivity/inattention, 4) peer relationship problems and 5) pro-social behavior. The SDQ further includes an impact supplement that asks if the registered behavior is considered a problem and if overall distress, social impairment, burden and chronicity are experienced. The SDQ is widely used to screen for mental health difficulties and as an outcome measure of psychological wellbeing both in clinical practice and in research. A total difficulties score is generated by adding scales 1-4 together and has been found to function as a dimensional measure of child mental health [10]. The questionnaire is available for parent and teacher reporting of children in four different age groups: toddlers (age 2 to 4 years), preschool children (age 5 to 6 years), school children (age 4 to 10 years) and adolescents (age 11 to 17 years). A self-report version is available for adolescents (age 11 to 17 years) [8]. All questionnaires are available in Danish and normative data from Denmark is available for children aged 5 to 12 years [11].

In the RCT, parental and staff reporting will be sampled. The use of multiple informants is commonly recommended to provide the most complete picture of the child’s psychological wellbeing and mental health, as parents and teachers observe children in different contexts, where different behaviors may be exhibited by the child [12]. For the cohort study, the self-report questionnaire is added when the children are aged 11 years or older. The SDQ will be administered electronically to parents and preschool staff twice yearly during preschool and to parents and teachers annually throughout the school years, with the addition of the self-report questionnaire when the child is 11 years of age and older.

The SDQ is expected to take around 10 minutes to complete.

Wellbeing is further measured using the KINDLR [13]. The KINDLR is a generic instrument for assessing health-related quality of life in children and adolescents (age 3 to 17 years). The KINDLR consists of six subdomains, each with four items. In this study, the subscales on physical wellbeing, emotional wellbeing and self-esteem are included (total of 12 items). During preschool, the KiddyKINDL-parents (age 3 to 6 years old) are used. Later, respective of age, parents’ report on the KiddyKINDL or the Kid- kiddoKINDL (age 7 to 17 years old), and children and adolescents report on the KidKINDL (age 7 to 13 years old) or the KiddoKINDL (age 14 to 17 years of age). Danish versions for children and adolescents age 7-17 are freely available. A Danish version of the KiddyKINDL- parents will be made following the instructions provided by the authors. The KINDLR will be administered at baseline and at follow-up as specified in the main protocol. The 12 KINDLR items are expected to take around 5 minutes to complete

The primary outcomes used for analyses in the RCT will be:

- Parent-reported psychological wellbeing, total difficulties score

Secondary outcomes used for analyses in the RCT will be:

- Staff-reported psychological wellbeing, total difficulties score
- Parent-reported wellbeing, total of physical and emotional subscale
- Parent-reported self-esteem

In the cohort study, the following outcomes will be added.

- Self-reported psychological wellbeing, total difficulties score*
- Self-reported wellbeing, total of physical and emotional subscale**
- Self-reported self-esteem**

* For children aged 11 years and older

** For children aged 7 years and older

